### Intervention

Palliat Rehab will be delivered by an occupational therapist in the Mater Hospital and a physiotherapist in St. Francis Hospice. It has been observed that rehabilitation is best described as a process containing specific actions
^
21
^, and for this reason, the bundle of interventions, based on individual rehabilitation needs, will be investigated rather than specific components. The occupational therapist and physiotherapist delivering Palliat Rehab will engage with the patients directly about their rehabilitation wants and needs and will construct individualised plans on a case-by-case basis. As the specific elements of each patient’s experience will vary, no set number of intervention sessions have been planned. The number of intervention sessions will depend on the patient’s health, their desire to continue with the service, and their ongoing connection with either the Mater Hospital and/or St. Francis Hospice. A description of the intervention service based on TIDIER criteria is available in the
*Extended data.*

### Outcomes

This case study will collect multiple outcome measures to describe the intervention, to explore the experiences of participants, and to assess the utility of particular quantitative measures for such an intervention. The quantitative outcome measures to be collected from consenting patient participants during the concurrent component are divided into three categories (demographic, service-usage, and health and symptom data) and are listed in
Table 2. By collecting these three categories of data, it is anticipated that this case study will be equipped to adequately describe the sample served, the experience of patients receiving the intervention, and the feasibility of embedding the service into the existing healthcare infrastructure using service-usage data. All quantitative data measures will be collected once following initial enrolment of each patient, with the exception of the Palliative Care Outcomes Collaborative (PCOC) scale, which will be collected at baseline during the first intervention session and repeatedly collected during each session thereafter.

**Table 2. T2:** Quantitative data and measures.

Demographic data	Service-usage data	Health and symptom data
1. Gender Identity 2. Age 3. Marital status 4. Primary diagnosis 5. Primary care network 6. Current living conditions including home supports	1. Response times between referral and service enrolment 2. The number, type, nd period of clinical interactions with the rehabilitative palliative care service 3. Length of hospital stay (for hospitalised patients only) 4. Whether re-admitted to hospital within 30-days of discharge or receipt of services enrolment 2. The number, type, and period of clinical interactions with the rehabilitative palliative care service 3. Length of hospital stay (for hospitalised patients only) 4. Whether re-admitted to hospital within 30-days of discharge or receipt of services	1. The Palliative Care Outcomes Collaborative (PCOC) scale ^ 22 ^ 2. Charlson Comorbidities Index (CCI) ^ 23 ^ 3. The Clinical Frail Scale ^ 24 ^ 4. Palmar Grip Strength 5. 5x Sit-to-Stand test ^ 25 ^

For the phased component, patients receiving Palliat Rehab will be asked if they are willing to contribute survey data based on their satisfaction with the service. Outcomes relating to the phased component of the case study also include the qualitative interview data collected from all three participant groups to effectively explore the general experiences and views of the service from the patient, informal caregiver, and staff perspective. 

### Sample size

The sample size for a case study depends on the number of participants that is sufficient to describe the phenomenon
^
18
^. As this case study design comprises two components, namely the concurrent component and the phased component, the rationale for each component’s sample size is described below.

### Concurrent Component

The aim of the case study is not to test the rehabilitation service, therefore it would not be appropriate to use traditional power calculations when considering sample size for the quantitative data collection component of the case study.
^
20
^ The purpose of quantitative data collection in the case study is to contribute to the understanding of care delivery and stakeholder experience and to test data collection instruments and examine the utility of selected outcome measures. Considering the issue of justification of sample adequacy, anonymised, routine data will be collected on all patients who receive the service. , and all eligible patients will be offered the opportunity to participate in survey data collection.

### Phased Component

Following the concurrent component, all patients who receive Palliat Rehab will be offered the opportunity to participate in a survey detailing their satisfaction with the service. The second element of the phased component refers to the qualitative interviews. As sample size estimation for qualitative interview samples is an area of conceptual debate and practical uncertainty
^
19
^, the projected sample size is based on the concepts of data adequacy and research practicality. The population included within this case study is relatively homogeneous, as participants will be availing of one single palliative care rehabilitation service. A sample of 16–22 individuals will therefore be recruited for qualitative data analysis across three stakeholder groups; patients receiving the service
*(n= 4*–6), family members of individuals receiving the service (
*n*= 4–6), and clinicians involved in the design and/or delivery of the new service (
*n*= 8–10).

### Recruitment

**
*Patients.*
** All potential participants will be provided with an information leaflet detailing the purpose of the data collection, the potential risks and benefits to participation, and data protection rights. Following a minimum of 24 hours, potential participants will be asked whether they are interested in being contacted by a researcher to discuss participation in the concurrent and phased components. Patients will be assured that they may receive Palliat Rehab through the concurrent component without further engaging in the phased component of the study. Once a patient receives input from the service, a researcher will make telephone contact with individuals who indicate that they are willing to be contacted and enquire if they are interested in participating in the phased component.

**
*Caregivers.*
** Patients receiving ‘Palliat Rehab’ will also be asked by either the physiotherapist, occupational therapist, or consultant to consider whether they wish for their primary caregiver to also be invited to participate in a separate Zoom or telephone interview. It will be explained that the reason for inviting their caregiver to participate is to include caregiver perspectives in the research study. It will again be emphasised that their decision or that of their caregiver will not influence the patient’s care in any way. Following a minimum of 24 hours and allowing sufficient time for the patient to discuss the matter with his/her caregiver, the patient will be asked whether their caregiver is interested in being contacted by a researcher to discuss participation. A researcher will telephone individuals who indicate that they are willing to be contacted and answer questions and provide information, as needed.

**
*Staff.*
** Clinical staff who have been involved in the design and/or delivery of the palliative care rehabilitation service will be invited to take part in two interviews by the Principal Investigator (PI). The researcher will provide the potential participant with written information on the study and the consent form and will be available to answer further questions, as needed. Both interviews will be separated by a minimum of 6 months to contrast learnings and applications of developed knowledge during the piloting of the intervention. It will be explained that the reason for inviting the staff member to participate is to include the perspectives of health and social care professionals in the study. Information will be provided to them regarding the study, the potential risks and benefits to participation, and data protection rights. It will be emphasised that the decision of the staff member will not influence or affect their career or work relationships in any way. If the staff member expresses interest in participating, the PI will send an individualised email introducing the staff member to the researcher.

### Data collection

Using a mixed-methods approach, multiple sources of quantitative data will be collected in a sequential manner. Quantitative data collection will take place from service commencement, while qualitative interviewing will take place at two points- approximately 4–6 months after commencement of the service and in the final two months of service provision.

**
*Quantitative data.*
** Quantitative measures will include data that is recorded as a necessary or usual part of palliative care or rehabilitative palliative care service provision during patient assessments in patient charts or electronic patient records. All quantitative measures are summarised in
Table 2 under three category headings: demographic data, service-usage data and, health and symptom data. Following the establishment of informed consent from patients, demographic, service use and health and symptom data necessary for the delivery of care will be collected by the service’s occupational therapist and/or physiotherapist. As part of the phased component, survey data on patient satisfaction will be collected on completion of engagement with the rehabilitation service intervention.

**
*Qualitative data.*
** Semi-structured interview schedules for the first set of interviews for each group of participants were developed using a five-step framework of design
^
26
^. The five steps are as follows: (1) identifying the prerequisites for using semi-structured interviews; (2) retrieving and using previous knowledge; (3) formulating the preliminary semi-structured interview guide; (4) pilot testing the guide; and (5) presenting the complete semi-structured interview guide. Interviews across all three participant cohorts may take place in person or remotely according to the participant’s preference. Only an audio recording will be made regardless of method of interview. Interviews are estimated to last approximately 30–40 minutes and protocols will be piloted with volunteers in St. Francis Hospice to ensure question clarity, in addition to monitoring time demand.

### Data management

Potential participants personal data will be processed under article 6 (1)(e) Public Interest and under article 9 (2)(j) Scientific Research of the General Data Protection Regulation (GDPR) 2016
^
27
^, and data will be secured in accordance with the requirements of the Data Protection Act (2015). Data will be anonymised and where applicable, pseudonyms will be used in reports and publications.

**
*Analytic plan.*
** Data analysis will be iterative and will continue over the course of the study.

Descriptive statistics will be generated using R
^
28
^ to summarize participant characteristics across demographic and service usage domains, where categorical variables will be reported as raw numbers and percentages. Reports of continuous variables will include mean, median, range and standard deviation values. For repeated measures analysis of health and symptom data pre- and post-service engagement, significance of variations will be determined using
*x
^2^
* tests or Fisher’s Exact Test, when required, for categorical data, Mann-Whitney U tests for ordinal data, and t-tests/ ANOVA for continuous data
*. 95%* confidence intervals (CI) will be used, and significance levels will be assessed at the alpha level of
*.05.*

Interview audio will be transcribed using Happy Scribe (2021) transcription software and reviewed using original audio-recordings to ensure accuracy, the removal of identifiable information and to engage in data familiarity. For qualitative data, reflexive thematic analysis
^
29–
31
^ will be used to generate descriptive themes related to the experiences and perspectives of stakeholders on the novel service. Thematic analysis was selected for analysis given its flexibility in application, enabling the collation of differing perspectives and the iterative construction of common themes.

Coding will be conducted both inductively and deductively using the open-source QDA Miner programme
*(version Lite),* where inductive coding will entail annotating similarities and intriguing features across the dataset. Deductive coding will comprise the construction of a deductive codebook based on the core foundations of the Adult Palliative Care Services Model of Care
^
2
^, and contemporary literature on rehabilitation, integration and palliative care
^
32–
34
^.

Coding will be completed by three researchers forming a coding team with diverse academic backgrounds in health economics, rehabilitative palliative care, and psychology. These researchers will not be involved in the provision of the rehabilitative service. Coding will be completed through individual coding sessions and facilitatory discussions to gauge differences in interpretation and to fully explore the breadth of data collected. As the dataset will be coded progressively, base codes will be continually revised and refined in response to new facets of data. Theme construction will then be facilitated by the design of a coding tree to identify similar concepts generated during the coding process. To ensure regular reflection during the analytic process, a reflexive log will be maintained to track and detail aspects of the coding process to identify potential assumptions underlying their approach
^
31
^. Qualitative analysis will be reported in line with the COREQ reporting guidelines
^
45
^.

The construct validity, internal validity, external validity, and reliability of the data will be established through use of the following methods. First, the use of a protocol and exact documentation of each step of the process facilitates traceability
^
35
^. Second, the use of multiple methods increases validity by providing multiple perspectives on the same phenomenon
^
35
^. Third, a researcher diary will be used to record thoughts, feelings, and expectations that may at a later stage be used for data analysis
^
36
^. Fourth, a well-structured database will be used for data management and will serve as the evidentiary source of conclusions
^
35
^. Fifth, analytical techniques during data analysis such as explanation building and addressing rival explanations will be employed
^
37
^. Sixth, the multidisciplinary composition of the team will allow the researchers to raise questions throughout the course of the study, particularly regarding the fit between the methods used and the results obtained, and study conclusions
^
37
^. Finally, thick description will establish transferability
^
38
^. Convergence of quantitative and qualitative data will be undertaken to describe the service and its implementation from the perspectives of patients, informal carers and clinicians.

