### Objectives

This is a protocol for a case study which will examine a palliative rehabilitation intervention. The specific study objectives are:

To describe the novel rehabilitative palliative care service that spans hospital and community settings.To explore the experiences of patients, informal carers and clinicians while receiving or providing the service.To test data collection instruments and examine the utility of selected outcome measures.

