## Discussion

Overall, this case study will examine Palliat Rehab by (i) outlining the structures and components of the integrated service, (ii) investigating the perspectives of key stakeholders, and (iii) analysing the chosen outcome measures for suitability in the intervention. Given the projected increases in both palliative care and rehabilitative needs among the Irish population over the next two decades
^
1
^, this case study is likely to uncover valuable insights into offering an accessible and integrated services to meet these growing demands. Moreover, Palliat Rehab will uphold the aims of Sláintecare reform in the Irish healthcare system, which seeks to achieve a universal single-tier health and social care system where everyone has equitable access to services based on need, and not ability to pay
^
53
^. Core Sláintecare goals are the achievement of a shift in care from the acute to the community setting to bring care closer to home for service users, and a focus on enablement and well-being. Palliative rehabilitation aligns well with these objectives as it seeks to integrate enablement, self-management, and self-care into the holistic model of palliative care.

Despite being recognised as an essential part of palliative care service provision
^
2
^, rehabilitation services remain under-developed and under-utilised in Ireland and beyond. New pathways and models of care are required to advance service provision to ensure that patients receive the ‘right care, in the right place, at the right time, by the right people’. The development of ‘‘Palliat Rehab’’ offers opportunity to study an innovative service and consider its potential contribution to the achievement of Sláintecare goals. Investigating the rehabilitation service in-depth and within its environmental context will lead to a better understanding of ‘how’ and ‘why’ things happen. Case study findings will be of value in assessing whether there is evidence that supports the rehabilitation service, and will be used to inform efforts to further develop and tailor the intervention.

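### Objective 3 asks about the utility of the outcome measures, but the only analysis specifically assigned to them is pre/post significance testing, which the schedule allows for PCOC alone

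*Protocol article*

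**What the plan says.** Under Objectives, the third aim is: "To test data collection instruments and examine the utility of selected outcome measures". The Concurrent Component part of Sample size repeats this as a purpose of the quantitative data. The Discussion restates it as "analysing the chosen outcome measures for suitability in the intervention".

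The same Concurrent Component text explains why there is no power calculation: "The aim of the case study is not to test the rehabilitation service".

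The Analytic plan (under Data management) assigns descriptive statistics "to summarize participant characteristics across demographic and service usage domains". The health and symptom domain is not named there. A further sentence is not tied to any domain: "Reports of continuous variables will include mean, median, range and standard deviation values". For the health and symptom data the plan then states: "For repeated measures analysis of health and symptom data pre- and post-service engagement, significance of variations will be determined using" chi-square or Fisher's exact tests (categorical), Mann-Whitney U (ordinal) and t-tests/ANOVA (continuous). It adds that 95% "confidence intervals (CI) will be used, and significance levels will be assessed at the alpha level of" .05.

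On timing, Outcomes says: "All quantitative data measures will be collected once following initial enrolment of each patient". The one exception is PCOC, taken at the first session and at each later one.

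Limitations says that the interviews will help to interpret what the quantitative outcomes mean.

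**The concern.** The named analysis answers a different question from the objective. A pre/post test asks whether scores moved while patients used the service. Utility asks whether patients can complete a measure, whether its scores spread over the scale or pile up at one end, and, for a repeated measure, how large the change is relative to its variability.

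This is more than detail that an article leaves to a fuller document. The article does fix an analysis for these measures, down to the test names and the alpha level. What it fixes does not match the stated objective, and for most of the measures the article's own schedule makes it impossible to run.

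At stake is whether the study can report quantitatively on one of its three objectives. Limitations calls the clinical usefulness of function and mobility measures in this population debated. Grip strength and the sit-to-stand test belong to that class, and neither has a second measurement.

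**Working it through.** The document gives no sample size, power or expected completion rate, so there is no figure to reproduce. The check compares the sections, followed by two illustrations on assumed inputs.

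**1. Schedule against analysis.** The measures are the five under health and symptom data in Table 2; the timing is from Outcomes.

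| Measure | Collected | Pre/post test possible | Completion and score distribution possible |
|---|---|---|---|
| PCOC | Baseline and every later session | Yes | Yes |
| Charlson index | Once | No | Yes |
| Clinical frailty scale | Once | No | Yes |
| Palmar grip strength | Once | No | Yes |
| 5x sit-to-stand | Once | No | Yes |

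The analysis specifically assigned to this domain can be run for 1 of 5 measures. Completion and score distribution can be reported for 5 of 5.

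**2. What else in the plan could serve objective 3.**
- The sentence on mean, median, range and standard deviation may extend to the health measures. It would show spread, and in part whether scores reach the scale ends. It would not show completion or the percentage at floor or ceiling.
- The 95% confidence intervals would show the precision of a PCOC change. They do not show completion.
- The qualitative appraisal can address meaningfulness. With 4–6 patient interviews planned (Phased Component), it cannot supply completion rates or score distributions. The planned convergence of the two data types is directed at describing the service and its implementation; the utility of the measures is not named there.

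**3. Does a pre/post p-value measure utility, even for PCOC?** For a paired t-test, t = SRM × √n on n − 1 degrees of freedom, where SRM (standardised response mean) is the mean change divided by the SD of change. Take the same observed SRM of 0.2 at several n (both assumed):

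| n pairs | t = 0.2 × √n | two-sided p |
|---|---|---|
| 20 | 0.89 | 0.38 |
| 50 | 1.41 | 0.16 |
| 100 | 2.00 | 0.048 |
| 200 | 2.83 | 0.005 |

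Responsiveness is identical in every row, yet the p-value crosses .05 because n grows. The SRM carries the information that the objective needs.

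**4. Is completion estimable at modest n?** The Wilson 95% interval is [p + z²/2n ± z√(p(1−p)/n + z²/4n²)] / (1 + z²/n), with z = 1.96 and an assumed completion rate p = 0.70:
- n = 30: (0.764 ± 0.176)/1.128 = 52% to 83%
- n = 50: (0.738 ± 0.133)/1.077 = 56% to 81%
- n = 100: (0.719 ± 0.092)/1.038 = 60% to 78%

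These intervals are wide at the smaller sizes, but they bear directly on the objective.

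**The case against.** Four points can be made for the plan.

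**The tests are not all that the plan offers.** It has confidence intervals, a general sentence on summary statistics and a qualitative route to meaningfulness, and the objective does not demand a purely quantitative answer. This stands. A reader might infer that objective 3 gets no answer at all, and the document does not support that. What remains is narrower: the quantitative data are said to serve this purpose, and no quantitative analysis is matched to it.

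**No rule judges a measure by its p-value.** This also stands. A reader might infer that a measure with a non-significant change would be called uninformative, and might then read the shortfall in power as a rate of wrongly discarded measures. The article states no criterion for keeping or dropping a measure. Any such rate would also need an assumed sample size and effect, and could apply only to PCOC. The p-value table in the working shows that significance is a poor index of responsiveness; it does not show that the plan would use it that way.

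**Completion and floor/ceiling summaries are details an article may leave out.** Taken alone, their absence would be no finding. The point rests on the mismatch between the analysis that is named and both the objective and the schedule.

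**Completion among participants would flatter the measures.** Table 1 excludes patients whom the attending clinician judges unable to complete them. In addition, Study status puts the start of collection in February 2020, so reasons for non-completion may not be recoverable for everyone. Both are fair, and the fix allows for them.

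**Conclusion.** The point holds in a limited form. The only analysis that the article specifically assigns to the health and symptom measures tests change under the service, which it says is not the aim. By its own schedule that analysis is feasible for one of the five measures. The other provisions help with spread, precision and meaning, but leave completion and floor/ceiling effects unreported.

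The size is therefore four of five measures with no specifically assigned analysis that can be run, and a fifth whose assigned test does not measure utility. This count rests on reading the single-collection statement under Outcomes literally. If second measurements are in fact taken for other measures, the feasibility part shrinks but the mismatch with the objective remains. The numerical illustrations rest on assumed n, SRM and completion rate, and the conclusion does not depend on them.

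The change is worth making because an explicit objective lacks a matching quantitative analysis and the remedy is cheap.

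**What to change.** State an objective-3 analysis in the Analytic plan. For each health and symptom measure in Table 2, report:

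- **(a) Completion:** number completed over number of patients for whom it was due, by setting (hospital, community), with a 95% CI. Give reasons for non-completion where the records show them. Report separately the number excluded under Table 1 as unable to complete the measures, so that completion among participants is not read as feasibility in all patients.
- **(b) Distribution:** score distribution, with the percentage at floor and ceiling where the scale has them.
- **(c) Change, PCOC only:** paired change and standardised response mean, each with a 95% CI.

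Say that utility will be judged from (a) to (c) together with the qualitative appraisal described under Limitations, and label any pre/post p-value exploratory. Reword the pre/post sentence so that it agrees with the collection schedule under Outcomes.

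The cost is one or two extra tables from data already being collected, with no new patients or assessments. Reasons for non-completion may be incomplete for patients already seen, and the report should say so.

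### The protocol says it does not test the service, yet it plans uncontrolled pre/post significance tests at .05 and looks to the findings for evidence supporting the service

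*Protocol article*

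**What the plan says.** Protocol article, Sample size, Concurrent Component: "The aim of the case study is not to test the rehabilitation service". It follows, in the authors' view, that "it would not be appropriate to use traditional power calculations when considering sample size for the quantitative data collection component". The quantitative data are meant to help understand care delivery and stakeholder experience, and "to test data collection instruments and examine the utility of selected outcome measures".

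Protocol article, Data management (Analytic plan): "For repeated measures analysis of health and symptom data pre- and post-service engagement, significance of variations will be determined using" chi-square or Fisher's exact tests for categorical data, "Mann-Whitney U tests for ordinal data, and t-tests/ ANOVA for continuous data". Confidence intervals at 95% are planned, and "significance levels will be assessed at the alpha level of" .05. The Abstract lists the same tests as part of the descriptive statistics.

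Protocol article, Discussion: "Case study findings will be of value in assessing whether there is evidence that supports the rehabilitation service".

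Three further places bear on the point. The Design section describes one service, run by one hospital and one community organisation over 18 months, with no comparison group. The Outcomes section says every quantitative measure is taken once after enrolment, except the PCOC scale, which is taken at the first session and at each later one. The Intervention section fixes no number of sessions; it depends on the patient's health, wish to continue and continuing link with either organisation.

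**The concern.** The absence of a test is the stated reason for not sizing the quantitative component, yet a test with a fixed decision level is planned. A pre/post significance test on patients' health data asks whether patients changed while using the service. Together with the Discussion sentence, it invites the reader to take a p-value below .05 as support for the service and one above .05 as lack of support.

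The design supports neither reading. Without a comparator, a change may come from disease progression, from the specialist palliative care that patients receive anyway, or from who remains in the service long enough to give a later score. Entry on an identified need makes regression to the mean possible as well. Without a planned sample size, a null result says little about whether change occurred. What is at stake is the conclusion drawn about the service and carried into the project report and later studies.

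**Working it through.** **1. Is there a planned figure to reproduce?** No. The only error-rate figure is the chosen level of .05. No quantitative sample size, power, effect size or sidedness is given.

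**2. The statements side by side.**

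| Place | Statement | Consequence |
|---|---|---|
| Sample size, Concurrent Component | The service is not being tested | No power calculation |
| Data management, Analytic plan | Pre/post change is tested at .05 | A decision rule on patient change |
| Abstract | The same tests are called descriptive | Inference labelled as description |
| Discussion | Findings help judge whether evidence supports the service | Findings pointed at effectiveness |
| Design | One service, no comparison group | Change cannot be assigned to a cause |

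The first row cannot stand with the second and fourth as written.

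**3. Which data can be compared pre/post?** Table 2 lists five health and symptom measures: PCOC, Charlson index, frailty scale, grip strength and 5x Sit-to-Stand. Under the Outcomes section only PCOC has a later value. The analytic plan nevertheless provides pre/post tests for categorical, ordinal and continuous health data. The two sections need to be reconciled.

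**4. What a pre/post test can and cannot show.** The expected mean change is the sum of any service effect and all other change (progression, concurrent care, selective follow-up, regression to the mean). With one group, only the sum is estimated. The test addresses whether the sum is zero, and the .05 level puts no limit on the non-service part.

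**5. Illustration. None of the inputs is in the protocol.** Assume a paired two-sided test at .05, a true mean change of *d* SD, within-patient correlation *r* = 0.5, and *n* patients with both values.

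- SD of the difference = √(2(1 − r)) = √(2 × 0.5) = 1.
- Chance of significance = Φ(d√n − 1.96) + Φ(−d√n − 1.96).
- Example: d = 0.3, n = 50: d√n = 2.121, and Φ(0.161) plus a negligible second term = 0.564.

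| n | d = 0.2 | d = 0.3 |
|---|---|---|
| 30 | 0.195 | 0.376 |
| 50 | 0.293 | 0.564 |
| 100 | 0.516 | 0.851 |

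The table reads two ways. If the whole change is unrelated to the service, these are the chances of a significant result with no service effect. If the whole change is due to the service, the chance of missing it is one minus the entry: for d = 0.2, 1 − 0.195 = 0.805 at n = 30 and 1 − 0.516 = 0.484 at n = 100. The test cannot tell the two cases apart, whatever values are assumed.

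**The case against.** The strongest reply is that this is an exploratory, mixed-methods case study which already shows caution. The Limitations section concedes that the measures may say little about effectiveness and that qualitative data will be used to interpret them. The Data management section promises to consider rival explanations. The Conclusion speaks of perceived effectiveness and of informing later interventional studies. Whether a measure moves during service engagement is also relevant to the third objective, the utility of outcome measures. A pre/post comparison is therefore not automatically an efficacy claim.

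Much of this stands. It is why deleting every test is not required, and why the point is one of reconciliation. It does not remove the contradiction. The Limitations section places the weakness in the measures, not in the missing comparator, and nowhere does the article say that uncontrolled change cannot be attributed to the service. Responsiveness of a measure can be shown by an estimate with its interval and needs no .05 rule.

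Three stronger readings may tempt a reader, and the document does not support them:

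- *Inflated false-positive risk from many items.* Only PCOC is repeated and its item count is not given, so any family-wise figure would rest on an assumed number of tests. The lack of a primary variable or multiplicity method is also no fault in an article on an exploratory study.
- *Repeated significance testing during the study.* The sentence "Data analysis will be iterative and will continue over the course of the study" heads a plan for both strands and fits the progressive qualitative coding described later. No interim significance tests are stated.
- *P-values used as proof that the service works.* The Discussion speaks of assessing whether there is such evidence, and of the findings of the whole case study.

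Regression to the mean is likewise a possibility only: referral is holistic and case by case, with no stated score threshold.

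**Conclusion.** The point holds in this form: the reason given for having no sample size (no test of the service) is contradicted by the planned pre/post tests at .05, and the Discussion directs the findings towards support for the service. With no comparator and no planned quantitative sample size, neither a significant nor a non-significant change can be attributed to the service or to its absence of effect.

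This rests on the text and on the single-group design, not on any assumed number. The size of the possible error cannot be derived from the documents. The illustrative range of roughly 20% to 85% for a significant result without a service effect depends wholly on the assumed drift, correlation and number of patients.

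This should be corrected, because it changes what the study may conclude. It does not threaten the descriptive or qualitative aims.

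**What to change.** 1. **Data management, Analytic plan.** Report pre/post change as within-patient paired estimates with the 95% confidence intervals already planned. Drop .05 as a decision criterion, or label any p-values exploratory.
2. **Outcomes and Data management.** Reconcile the two. As the Outcomes section stands, the pre/post analysis covers PCOC only; if other measures are recorded again, say which.
3. **Abstract.** Align the analysis sentence with item 1, so that tests are not presented as descriptive statistics.
4. **Limitations.** Add that there is no comparison group and that uncontrolled change is not evidence of a service effect.
5. **Discussion.** Reword the sentence on evidence for the service, so that the quantitative findings guide the choice of measures and the design of later intervention studies, as the Conclusion already indicates.

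Cost: wording only, provided that item 2 is settled by limiting the comparison to PCOC; no new data are then needed. The study gives up a significance claim that its design cannot support.
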